### 2.11. Administrative and Oversight Information

This manuscript describes version 1.0 of the ALMA trial protocol, dated June 2026. The trial is registered at ClinicalTrials.gov under the identifier NCT07165912. The trial registry record will be kept consistent with the final approved protocol, including the study design, target sample size, intervention arms, eligibility criteria, outcome measures, and assessment time points.

The Principal Investigator will be responsible for the overall coordination of the trial, protocol implementation, supervision of recruitment, safety reporting, data integrity, and communication with the Research Ethics Committee. The oncology team will identify potentially eligible participants during routine clinical care. The principal researcher will obtain informed consent, administer baseline and post-intervention assessments, maintain study documentation, and monitor adherence. The principal researcher will be responsible for the intervention and deliver the ALMA sessions according to the intervention manual and will document attendance, adverse events, and protocol deviations.

There is no external or commercial sponsor for this study. The University of Salamanca will provide institutional oversight in accordance with applicable ethical, legal, and institutional requirements.

Given the low-risk, non-pharmacological nature of the ALMA intervention and the individual cognitive training programme, no independent Data Monitoring Committee will be established. The Principal Investigator and authorized members of the research team will conduct trial monitoring internally. Monitoring activities will include periodic review of recruitment progress, eligibility documentation, informed consent forms, adherence records, intervention attendance logs, adverse event reports, protocol deviations, withdrawal reasons, and completeness of outcome assessments.

No routine external auditing is planned. However, essential study documents may be reviewed by the University of Salamanca, the Research Ethics Committee, or other competent institutional authorities if required. Documents available for review may include the approved protocol and amendments, ethics approval documentation, informed consent forms, screening and enrolment logs, randomization and allocation records, adverse event logs, protocol deviation records, data management logs, and pseudonymized datasets.

### 2.12. Intervention Materials

The intervention materials were designed to reflect the specific objectives of each study arm and to support consistency in intervention delivery. Figure 2 provides an overview of the materials used in G0, G1, and G2, highlighting the psychoeducational, cognitive, ecological, compensatory, and group-based components of the ALMA intervention.

G0 (Health Education): Participants will receive informational support through standardized leaflets. These materials are based on WHO guidelines and provide evidence-based recommendations on healthy lifestyles, self-care, and risk-reduction practices to mitigate cognitive decline.G1 (Cognitive Training): This group utilizes individual dossiers focusing on tasks that simulate Instrumental Activities of Daily Living (IADL). These activities require the integration of multiple cognitive functions, including attention, reasoning, working memory, planning, and processing speed. Specific functional contexts include medication adherence, meal preparation, financial management, and the use of communication technologies.G2 (ALMA): The experimental group employs a specialized cognitive intervention framework designed to target all major cognitive domains. This intervention requires a diverse array of multisensory and multimodal materials, including audiovisual support, specialized notebooks, and various stationery (e.g., colored pencils, scissors, and photos).

The use of these materials is intended to support ecological validity by linking cognitive exercises to everyday activities relevant to women with breast cancer.

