#### 2.6.2. Cognitive Training Group (CT) G1

Participants in the Cognitive Training (CT) group (G1) will undergo a structured programme focused on everyday cognition, administered individually to each patient. The intervention will be delivered through a meticulously developed dossier designed specifically for the objectives of this study. Notably, all participants in this arm will receive identical tasks, with no individualized adaptations for difficulty level or functional profile.

The intervention is structured into four consecutive one-month training periods (P1–P4), totaling 80 activities (20 activities per period). Participants are required to complete five activities per week. To monitor treatment adherence and ensure compliance with therapeutic guidelines, a dual follow-up system will be implemented:Remote Follow-up: Conducted via video call at the conclusion of P1 and P3 (Months 1 and 3).In-person Follow-up: Conducted at the clinic at the conclusion of P2 and P4 (Months 2 and 4) to evaluate progress and address emergent concerns.

The final evaluation for G1 will coincide with the completion of the fourth training period (P4). This group serves to control the effects of cognitive stimulation and professional monitoring without the specific multimodal components of the ALMA.

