### 3.3. Secondary Outcomes

Secondary outcomes will include subjective cognitive function, everyday cognition, functional autonomy, anxiety, sleep quality, performance status, and everyday memory failures.

Functional Assessment of Cancer Therapy-Cognition (FACT-Cog), Version 3: To assess patient’s perceived cognitive functioning and its impact on quality of life. The FACT-Cog assessment is composed of 37 item questionnaires, which are divided into six cognitive domains: memory, concentration, mental acuity, verbal fluency, functional interference, and multitasking ability. The scale is composed of three subscales: symptoms of perceived cognitive impairment, where a higher score indicates fewer symptoms; perceived cognitive abilities, where a higher score indicates superior cognitive skills rating; and overall quality of life, where a higher score indicates an enhanced quality of life relative to cognition [31]. Validated in Spanish oncology cohorts, it demonstrates exceptional internal consistency α = 0.93 for the global scale α = 0.90 for the CogPCI subscale) and a test–retest reliability coefficient of r = 0.84. Higher total or subscale scores indicate fewer subjective cognitive complaints and a higher cognitive-related quality of life. The MCID for the total score ranges between 6.9 and 10.6 points (and 4.6 points specifically for the CogPCI subscale) to establish a clinically meaningful therapeutic improvement.The Test for the Assessment of Everyday Cognition (PECC) is a standardized instrument designed to evaluate an individual’s capacity to manage day-to-day activities. The PECC assesses an individual’s ability to solve 12 real-life scenarios, which are grouped into the following domains: medication, administrative management, financial management, food preparation, transportation, and shopping. The PECC provides a comprehensive assessment of an individual’s functional capacity in daily living activities, thereby providing valuable insights into their overall cognitive abilities and daily living skills. The administration time is 35 min [32]. Normatively validated in Spain for adult populations, the PECC demonstrates an excellent inter-rater reliability with an Intraclass Correlation Coefficient (ICC) of 0.94, alongside robust ecological validity. Scores are calculated continuously per domain and then aggregated, where higher cumulative scores denote superior objective functional autonomy. A statistically significant post-intervention increase relative to the control group demonstrates successful clinical transfer of trained cognitive strategies to the patient’s actual environment.The Lawton and Brody Scale is a tool designed to evaluate autonomy in instrumental activities of daily living. The administration time for this assessment is four minutes. It measures 8 semi-complex tasks: telephone use, shopping, food preparation, housekeeping, laundry, mode of transportation, responsibility for own medications, and financial management. Each item is scored binary as either 0 (dependent) or 1 (independent), yielding a total score from 0 to 8 in women [33]. It exhibits high cross-cultural reproducibility with a Guttman scalogram coefficient of 0.96. A total score of 8 indicates complete functional independence. Any score <8 establishes functional decline. Therapeutic success is operationalized as the preservation of maximum baseline autonomy (score of 8) or a reduction of dependency indicators post-chemotherapy.The Hamilton Anxiety Scale is a psychometric instrument that is employed to evaluate the severity of anxiety in patients who meet criteria for anxiety [34]. The scale consists of 14 items, each with five response options ranging from “not present” to “very severe” with a total score range of 0 to 56. The adapted Spanish version demonstrates high internal consistency (α = 0.89) and inter-rater reliability (r = 0.94). Clinical severity thresholds are categorized as: ≤17 (mild anxiety), 18–24 (mild-to-moderate anxiety), and 25–30 (moderate-to-severe anxiety). The MDC for this instrument is 4 points; thus, a post-intervention decrease of ≥4 points confirms a statistically reliable and clinically significant therapeutic reduction in anxiety.The Pittsburgh Sleep Quality Index (PSQI) was developed to assess sleep quality in individuals between the ages of 24 and 83. This instrument requires approximately 5 to 10 min for completion. The study’s objective is to assess the impact of subjective sleep quality, sleep latency, sleep duration, habitual sleep efficiency, sleep disturbances, sleep medication use, and daytime dysfunction on a total of 19 individual items [35]. Validated in Spanish oncology settings, it displays an internal consistency of α= 0.81 and high diagnostic sensitivity (89.6%). A global score >5 serves as the clinical cut-off point, separating “good sleepers” from “poor sleepers” (chronic sleep pathology). The MDC is 2 points, meaning a downward shift of ≥2 points post-intervention establishes a clinically relevant improvement in sleep hygiene.The Performance Status Scale (ECOG): Is a standardized scale used to evaluate the functional status of cancer patients and assess their ability to perform activities of daily living. It allows for an assessment of the disease’s impact on the patient’s functional status and helps guide therapeutic and prognostic decisions. The scale classifies functional status on a scale of 0 to 5. The numeral 0 indicates Patient is fully active, with no restrictions on performing daily activities;1: Limited ability to perform physically strenuous activities, but capable of light or sedentary work; 2: Capable of self-care, though unable to perform work activities; remains active more than 50% of the day; 3: Limited capacity for self-care; remains in bed or a chair more than 50% of the day; 4: Completely disabled; totally dependent for self-care; 5: Death. This scale ensures tight control over confounding physical decline during the trial; maintaining a Grade 0 or 1 throughout the study indicates clinical stability. [36].The Everyday Life Memory Failures (MFE) Questionnaire is a tool designed to assess various forms of memory impairment, a 28 item self-report instrument designed to evaluate the subjective frequency of cognitive lapses and minor memory failures occurring within the patient’s typical daily environment. Respondents rate each item on a 5-point Likert scale (0 = never to 4 = very often), with total scores ranging from 0 to 112. It encompasses a range of categories, including verbal memory, reading aptitude, writing skills, recognition of names, faces, and actions, as well as the ability to learn new information. The response to this question is measured using a Likert scale, which provides nine possible responses ranging from “Not once in the last 3 months” to “More than 1 time a day” [37]. The Spanish version exhibits a robust internal consistency (α= 0.89) and a stable test–retest reliability (r = 0.83). Higher cumulative scores reflect a higher density of daily cognitive failures, with normative healthy adult data averaging scores of 20–25. Consequently, a downward change score (Δ MFE < 0) post-intervention demonstrates an increase in perceived daily cognitive control and efficiency.

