### 4.2. G1 and G2

The comparison between G1 and G2 is intended to examine whether the multidimensional and group-based ALMA format provides additional value beyond individual cognitive training. Both groups include cognitive activity, but they differ in delivery format, intensity of therapeutic contact, group interaction, and integration of psychoeducational and ecological components.

G1 is based on the principle that structured and repeated cognitive practice may support specific cognitive domains such as attention, memory, reasoning, and executive functioning. Individual cognitive training activities, including paper-and-pencil exercises, represent a feasible approach to cognitive rehabilitation in cancer survivors [21,23,39,41]. This format allows participants to work individually and at their own pace, without the influence of group dynamics.

By contrast, G2 addresses CRCI from a multidimensional perspective by combining psychoeducation, cognitive stimulation, ecological task practice, compensatory strategies, and group feedback. The group-based format may provide social support and may contribute to emotional regulation, perceived coping, and engagement, which are relevant factors in the experience of cancer-related cognitive impairment [23,24,38,39,40,41,42].

The difference in therapeutic contact and social support between G1 and G2 may introduce performance bias. However, this discrepancy is deliberate, as it enables an analysis of effectiveness and feasibility in a clinically realistic intervention format. The use of intention-to-treat analysis and linear mixed models will allow adjustment for individual variability and within-participant correlation over time. This comparison will help assess whether the multidimensional and group-based ALMA format is associated with greater improvement than individual cognitive training alone.

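### The planned G2–G1 comparison on the PECC mixes practice on trained contexts with transfer: three of the six PECC domains are named training contexts of the G1 dossier

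*Protocol article*

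**What the plan says.** **G1.** Under Section 2.6.2, participants "will undergo a structured programme focused on everyday cognition, administered individually to each patient". The programme has 80 activities over four one-month periods. Section 2.12 describes the dossier as simulated instrumental activities of daily living: "Specific functional contexts include medication adherence, meal preparation, financial management, and the use of communication technologies".

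**PECC.** Section 3.3 describes 12 real-life scenarios "grouped into the following domains: medication, administrative management, financial management, food preparation, transportation, and shopping". Scores are calculated per domain and then aggregated. The reading rule is: "A statistically significant post-intervention increase relative to the control group demonstrates successful clinical transfer of trained cognitive strategies". Section 2.5 defines the control group as G0.

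**Comparisons.** Section 3.9 plans G2 versus G0 and G2 versus G1 for the secondary outcomes, everyday cognition included. G1 versus G0 is exploratory if reported.

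**ALMA.** Section 2.6.3 lists memory, executive function, attention, language and reasoning, and also speaks of ecologically valid activities. The Figure 2 legend and Section 4.2 add everyday-task material and practice. The everyday contexts are not named; Section 2.6.3 refers operational detail to Supplementary Material S1, and an intervention manual is planned.

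**G1 against G2.** Section 4.2 says of the two arms that "they differ in delivery format, intensity of therapeutic contact, group interaction, and integration of psychoeducational and ecological components".

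**The concern.** The Discussion gives the PECC the task of showing whether cognitive gains reach daily situations. The Limitations section leans on it as a supplement to the MoCA, which may have a ceiling. Its reading therefore carries the trial's secondary conclusion on everyday function.

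A test shows transfer only where it samples situations that were not themselves practised. If an active arm practises the contexts that the test scores, a gain in that arm may be practice. In the G2–G1 comparison, a null or negative PECC result could then be taken as no added benefit from ALMA when G1 had rehearsed part of the test content. In the G2–G0 comparison, a gain in a domain that ALMA itself trains would be labelled transfer under the Section 3.3 rule. The article does not discuss the overlap.

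**Working it through.** **1. Contexts side by side** (Section 3.3 against Sections 2.12 and 2.6.3 and the Figure 2 legend)

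| PECC domain | Named for G1 | Named for ALMA |
|---|---|---|
| Medication | yes | not stated |
| Financial management | yes | not stated |
| Food preparation | yes | not stated |
| Administrative management | no | not stated |
| Transportation | no | not stated |
| Shopping | no | not stated |

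The overlap is 3 of 6 PECC domains and 3 of the 4 contexts named for G1; the fourth, communication technologies, is not a PECC domain. Section 2.12 says the contexts *include* these four, so three is a minimum. The article does not say how the 12 scenarios divide among the domains, so half of the domains need not be half of the score.

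**2. Which comparison is touched**

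- G2 versus G1: G1 content overlaps the test. ALMA's overlap is unknown.
- G2 versus G0: the G1 dossier plays no part and G0 receives only a leaflet. Only ALMA's own everyday tasks matter.
- G1 versus G0: overlap is present, but this comparison is exploratory.

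**3. Size, as illustration only**

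The article gives no PECC standard deviation, effect or power, so there is no planned figure to reproduce. Assume equal domain weights and effects in SD units. Let *D* be ALMA's general gain on all six domains, *g* the G1 practice gain on the three shared domains, and *h* an ALMA practice gain on *k* domains. Then

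G2 − G1 = *D* + (*k*/6)*h* − (3/6)*g*.

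With no ALMA practice (*k* = 0) this is *D* − 0.5*g*. Power is for a two-sample t-test with 21 per arm, two-sided 0.05, no dropout and no multiplicity correction:

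| *g* | Difference, *D* = 0.5 | Power | Difference, *D* = 0.85 | Power |
|---|---|---|---|---|
| 0 | 0.50 | 35% | 0.85 | 77% |
| 0.3 | 0.35 | 20% | 0.70 | 60% |
| 0.6 | 0.20 | 10% | 0.55 | 41% |
| 1.0 | 0.00 | 5% | 0.35 | 20% |

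Now let ALMA practise too, with *h* = *g* = 0.6 and *D* = 0.5:

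- *k* = 0: 0.50 − 0.30 = 0.20
- *k* = 3: 0.50 + 0.30 − 0.30 = 0.50
- *k* = 6: 0.50 + 0.60 − 0.30 = 0.80

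The same G1 overlap can thus understate ALMA's general gain, leave it unchanged or overstate it. The missing input is ALMA's content.

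**4. Wording of the arms**

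Section 4.2 counts the integration of ecological components among the differences between G1 and G2, and the Figure 2 legend lists everyday tasks for G2 only. Sections 2.6.2 and 2.12 make G1 the programme built on everyday cognition and simulated daily tasks. These descriptions do not sit together.

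**The case against.** The strongest reply has five parts.

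- **The transfer rule names the control group, which is G0.** This stands. The rule does not declare a G2–G1 difference to be transfer, and the G1 dossier cannot distort G2 versus G0. The rule remains too strong for domains that ALMA trains.
- **The asymmetry is not shown.** This stands. A reader might infer that the PECC favours G1, because only G1's contexts are named. ALMA has everyday tasks too, and step 3 shows that the direction can go either way.
- **Shared labels are not shared items.** This stands. A reader might call G1 trained to the test, but the article shows common contexts in half of the domains and no common items.
- **The protocol already disclaims isolating components.** Section 4.1 says findings reflect intervention packages, and Section 4.2 speaks of integration, which does not say that G1 has no ecological content. This limits the wording problem to an inconsistency of description; it does not settle what a PECC difference means.
- **Sub-scores are commonly left to the analysis plan, and a three-domain score is weak.** The second half stands and is why the total should be kept. The first half does not dispose of the point, because the reading rule and the arm descriptions are fixed in this article.

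**Conclusion.** The point holds in a limited form. At least three of the six PECC domains are named training contexts in G1, ALMA's own contexts are not named, and G2 versus G1 on this outcome is planned. The aggregate result of that comparison therefore cannot separate practice from transfer, and a null or negative finding would be ambiguous.

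A reader might go further and conclude that the comparison can never support transfer. The documents do not bear that out: if ALMA has little matching practice, G2 exceeding G1 despite G1's practice would be conservative evidence in ALMA's favour.

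The direction and size of any bias are unknown. The SD-based figures rest wholly on assumed gains, equal domain weights and treating averaged domain effects as SDs of the total; they show the mechanism and estimate nothing. The MoCA primary endpoint is not affected. This is a cheap improvement to the reading of one secondary outcome.

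**What to change.** 1. Keep the validated six-domain PECC total as the secondary outcome.
2. Before group labels are revealed to the statistician, classify each PECC domain as trained or untrained in each arm, using the full G1 dossier and the ALMA manual. The named contexts alone are not enough, because the Section 2.12 list may be incomplete.
3. Pre-specify a supportive analysis of trained and untrained sub-scores, from the per-domain scores already collected, for G2 versus G1 and G2 versus G0. If the manuals leave no domain untrained in both arms, say so and make no transfer claim from the G2–G1 comparison.
4. Reword the Section 3.3 rule so that transfer is claimed only when the untrained domains support it; report gains in trained domains as possible practice.
5. Reconcile Section 4.2 and the Figure 2 legend with Sections 2.6.2 and 2.12 on the everyday-task content of each arm.

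The cost is some wording, one content comparison of the two manuals and one extra scoring step, with no new data. The drawback is that the sub-scores are less reliable than the total and imprecise at 21 per arm, so they can qualify the conclusion but should not replace the total.

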## 3. Outcome Measures

The effects of the ALMA compared to Cognitive Training (G1) and Health Education (G0) will be evaluated through a comprehensive battery of validated instruments. All assessment tools have been used in clinical or oncological research and validated Spanish versions will be used where available.

Evaluations will be conducted at baseline (T0) and upon completion of the four-month intervention (T1). In order to facilitate the interpretation of the study’s outcomes, Table 3 presents the primary and secondary outcome measures, the instruments that will be used for assessment, the evaluation time points, the scoring direction of each scale, and the direction of change considered to indicate improvement from baseline (T0) to post-intervention (T1).

